#### Secondary endpoints

The rate of all-cause hospital readmission, as defined in the primary endpoint, within 30 days after the patient discharge from the initial hospitalization.The rate of all-cause emergency department visits occurring within 30 days after the patient discharge from the initial hospitalization. This is the proportion of emergency department visits.The rate of all-cause mortality occurring within 30 days after the patient discharge from the initial hospitalization. This is the proportion of deaths.The number of consultations scheduled or not within 30 days post-hospitalization will be studied. Consultations are defined as interviews with the attending physician, a specialist physician or a nurse.Patient satisfaction with regards to its drug treatment will be measured using the standardized questionnaire “Satisfaction with Medicines Questionnaire (SatMed-Q®)” [21] validated in French [22]. It includes 17 items related to 6 different aspects: effectiveness, adverse effects, ease of use, patient's general opinion, treatment effect on daily life, quality of monitoring and information provided by health professionals. Answers are expressed on a 5-point Likert scale from "Not at all" to "Yes, a lot." There are six scores and an overall score (0 to 100). The evaluation will be conducted at 30 days post-hospitalization during the telephone follow-up.

### Follow-up and data collection

The evaluation will be performed at three different time points: baseline (T1), discharge at the hospital (T2) and 30 days after discharge from the hospital (T3). The study procedure and date collection are detailed in Table 3 and have been established as per the SPIRIT guidelines. A clinical research associate will collect the data with the clinical pharmacist. They will be obtained from the analysis of institutional documents of the medication reconciliation between admission and discharge and telephone follow-up documents 30 days after discharge.

**Table 3 Tab3:** Study procedure

	T1	T2	T3
Consent	X		
Randomization	X		
Satisfaction		X	
All-cause hospital readmission			X
All-cause emergency department visits			X
All-cause mortality			X
Consultations			X

*T1* baseline, *T2* discharge at hospital, *T3* 30 days after discharge hospital

### Data protection

As regards the computerized processing of data relating to this project, which is intended for health research, it falls within the scope of legislative requirements, in particular the law of 9 August 2004, and will directly or indirectly identify the persons concerned.

### Statistical considerations

#### Sample size, power and statistical methods

The calculation of the required number of subjects was made from the primary endpoint, i.e., the rate of re-hospitalization and/or death.

Based on the literature, mainly a recent meta-analysis including the RCTs working on a pharmacist-led medication review [11], and data provided by the medical information service, the expected proportion of re-hospitalization and/or death in the standard group is 20% (worst case scenario). To detect a difference of at least 6% between the two groups (i.e., 14% re-hospitalization of the experimental group) given a two-sided significance level of 5% and 80% power, 1300 patients are needed (650 in each group). To prevent 10% dropout, a total of 1400 subjects should be included. The recruitment will be open for 18 months, and we expect to recruit about 75 patients per month.

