**Methods/design:**

The study is a randomized controlled clinical trial. A total of 1400 hospitalized patients will be randomized in two groups: (1) the experimental group (group receiving a pharmacist-led medication review) and (2) the control group (group receiving usual care). The pharmacist-led medication review process includes medication reconciliation, treatment review and medication liaison service. The primary endpoint will be the rate of readmissions and/or death at 30 days following initial hospitalization discharge. The secondary endpoints will be the rate of hospital readmission, the rate of emergency department visits, the rate of mortality, the number of consultations and patient treatment satisfaction at 30 days following initial hospitalization discharge.

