### Randomization

Computer-generated randomized lists will be drawn up before the beginning of the study using a permuted block design under the responsibility of the clinical research unit (AP-HM). The randomization will be stratified by center. The patients will be randomized to the control group or the experimental group using a computer-generated randomization schedule with a 1:1 allocation ratio. The open-label study is the only option because of the involvement of the patient in the medication reconciliation procedure.

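### Including 1400 patients does not leave the required 1300 after the stated 10% dropout; it covers about 7% (minor, to be restated)

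*Protocol article*

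**What the plan says.** All the figures stand in one section of the protocol article, Sample size, power and statistical methods.

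- Assumed control rate: "the expected proportion of re-hospitalization and/or death in the standard group is 20% (worst case scenario".
- Target difference: "To detect a difference of at least 6% between the two groups (i.e., 14% re-hospitalization of the experimental group".
- Error rates: "given a two-sided significance level of 5% and 80% power".
- Requirement before losses: "1300 patients are needed (650 in each group".
- Allowance for losses: "To prevent 10% dropout, a total of 1400 subjects should be included".
- Recruitment forecast: "The recruitment will be open for 18 months, and we expect to recruit about 75 patients per month".

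The abstract repeats the total: "A total of 1400 hospitalized patients will be randomized in two groups". The Randomization section sets a "computer-generated randomization schedule with a 1:1 allocation ratio".

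The Data analysis section compares the day-30 proportions by chi-square or Fisher's exact test and does not impute missing data. The article does not say which formula or test gave 650 per group, or how 1400 was obtained from 1300 and 10%.

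**The concern.** An allowance for dropout should leave the required number once the stated fraction has been lost. Here the required number, the fraction and the inflated total are all printed, and the third does not follow from the other two. A reader who relies on the section would believe that the trial keeps its 80% power at 10% loss. Whether it does depends on a calculation basis that the article does not name.

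The loss matters because missing outcomes are not replaced, so a patient with no day-30 outcome adds nothing to the primary comparison. That outcome is collected by a telephone call 30 days after discharge, so some loss is to be expected.

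**Working it through.** **Inputs**, all from the protocol article: p1 = 0.20, p2 = 0.14, difference d = 0.06, two-sided alpha 0.05 (z = 1.960), power 0.80 (z = 0.842), 1:1 allocation, 1300 required, 10% dropout, 1400 to be included, 18 months, about 75 per month.

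**Step 1. Reproduce 650 per group.** With mean proportion 0.17:

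- Uncorrected chi-square: n = [1.960 × √(2 × 0.17 × 0.83) + 0.842 × √(0.20 × 0.80 + 0.14 × 0.86)]² / 0.06² = 614.1, so 615 per group or 1230 in total.
- Continuity-corrected: n′ = (n/4) × [1 + √(1 + 4/(n × d))]² = (614.1/4) × [1 + √(1 + 4/36.84)]² = 647.0 per group, or 1294 in total.

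The continuity-corrected result agrees with the stated 650 after rounding. The uncorrected one does not, nor do the unpooled-variance (612) and arcsine (611) versions. The figure of 1300 is therefore sound on the corrected basis, but that basis is inferred from the match and is not stated.

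**Step 2. Apply the stated dropout.**

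- Left after 10% loss: 1400 × 0.90 = 1260, and 1300 − 1260 = 40 short.
- Loss that 1400 does cover: 1 − 1300/1400 = 7.1%.
- Total that would leave 1300: 1300/0.90 = 1444.4, rounded up to 1445.
- Simpler inflation: 1300 × 1.10 = 1430.

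**Step 3. Power for 20% against 14%.** Uncorrected: Φ{[d − 1.960 × √(2 × 0.17 × 0.83/n)] / √[(0.16 + 0.1204)/n]}. The corrected version subtracts a further 1/n from d. At n = 630 this is Φ(0.0185/0.0211) uncorrected and Φ(0.0169/0.0211) corrected, using rounded values.

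| Evaluable (per group) | Uncorrected chi-square | Continuity-corrected | Fisher's exact |
|---|---|---|---|
| 1300 (650) | 82.2% | 80.2% | 80.4% |
| 1260 (630) | 81.0% | 78.9% | 79.1% |

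A 10% loss from 1400, compared with the intended 1300, costs 1.2 to 1.3 percentage points on each basis.

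**Step 4. Side note on recruitment.** 18 × 75 = 1350, which is 50 below 1400. Reaching 1400 needs 1400/18 = 77.8 per month, or 1400/75 = 18.7 months.

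**The case against.** Four points can be made for the plan.

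1. *The 80% target is still met with the ordinary chi-square test.* The Data analysis section names chi-square or Fisher's exact test and mentions no continuity correction. Without one, 1230 patients are enough, and 1260 give 81.0%. This stands, and it makes any shortfall in power conditional on the test. It does not make 1400 the right total for a requirement of 1300 with 10% loss.

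2. *The gap is small beside the uncertainty in the planning rate.* The same 6-point difference at 19% against 13% gives, at 630 per group, 80.8% corrected and 82.8% uncorrected. One point in the control rate moves power by about as much as the whole discrepancy. This stands and limits the importance of the point.

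3. *Not every dropout is lost.* The full analysis population keeps all randomised patients evaluated at baseline. A patient who leaves the intervention but is reached at day 30 still counts. This stands too, so the relevant 10% is loss of the day-30 outcome.

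4. *1400 may be 1430 rounded down.* That is plausible, but rounding down still leaves fewer than 1300.

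A reader might also infer that the trial will enrol only 1350 and end with 1350 × 0.90 = 1215 evaluable patients, with power of 77.3% (corrected) or 79.6% (uncorrected). The article does not support that. The rate is a rounded forecast, 77.8 per month is only 3.7% above 75, and nothing says that recruitment stops at 18 months if it is short of 1400. The 1215 figure holds only on the assumption of exactly 75 per month and closure at 18 months.

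**Conclusion.** The statement is wrong as written, and the error is minor. The 1300, the 10% and the 1400 cannot all hold: 1400 leaves 1260 after 10% loss, or covers 7.1% loss if 1300 are to remain. This rests only on printed figures and needs no assumption.

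The consequence for power does rest on one. If 650 per group came from a continuity-corrected calculation, as the reproduction suggests, power at 10% loss is about 79%, just under the stated 80%. With the uncorrected chi-square test it is 81%. Both figures take 20% against 14% as given and count 10% as lost day-30 outcomes. It would go too far to read this as a trial that is materially underpowered for the 6-point difference.

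The recruitment forecast is a side note: about 1350 against 1400 is a loose fit and does not count as a second error of the same kind.

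**What to change.** Restate the figures and keep the total at 1400. Suggested wording: *1400 randomised patients allow for about 7% loss of the day-30 outcome. With 10% loss, 1260 are evaluable, and power for 20% against 14% is about 79% (continuity-corrected, the basis that gives 650 per group) or 81% (uncorrected chi-square).* Keep whichever basis was used and name the test behind 650 per group.

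In the same paragraph, the sponsor should reconcile the forecast with the target, either with figures that reach it (about 78 per month for 18 months, or about 19 months at 75), if the sponsor considers them achievable, or by saying that recruitment continues until 1400 are included.

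The cost is a few lines of text. No extra patients are needed and the planned analysis does not change. The only price is that, on the corrected basis, the stated power at 10% loss becomes slightly less favourable than 80%.

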#### Data analysis

The major principles of the analysis are reported below. However, a specific protocol of the analysis will be provided a second time before the initialization of the study (validated by the investigator coordinator, the person responsible for the analysis, and the biostatistician). The data will be analyzed using SPSS version 17.0 software. Statistical significance is defined as *p* < 0.05. The methodology is based on the Consolidated Standards of Reporting Trials Statement (CONSORT, http:// www.consort-statement.org/consort-statement/) [23].

The full analysis population (including all subjects who will be randomized and at least evaluated at the baseline) will be used in the primary analysis, and the per protocol population (including all subjects who will be randomized and will not have major protocol deviations) will be used in the secondary analysis to assess the robustness of the results. No interim analysis is planned. Demographic and baseline characteristics will be summarized for the two groups (‘standard’ and ‘experimental’ groups). Missing data will not be replaced.

Primary endpoint. The proportions of readmission and/or death at day 30 will be compared between the two groups (chi^2^ test or Fisher’s exact test). Proportions will be presented with 95% confidence intervals. Logistic regression will be performed to adjust potential confounding factors; variables relevant to the models will be selected based on their clinical interest and/or a threshold *p*-value ≤ 0.1 during univariate analysis. The center will be automatically entered into the model. The final models expressed the odd ratios and their 95% confidence intervals. The unadjusted analysis will be the primary analysis, and the adjusted analysis will be the complementary analysis.

Secondary endpoints. Qualitative variables will be compared between the two groups using the same procedure. The number of consultations and satisfaction scores will be compared between the two groups using Student’s *t* test or Mann-Whitney test. Multivariate approaches (logistic or linear regressions) will be performed using the same procedure.

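### Covariates for the complementary adjusted models are screened by univariate p ≤ 0.1 in the trial's own data, so those models are not fixed in advance

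*Protocol article*

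**What the plan says.** All of this stands in the Protocol article, under Data analysis.

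- Purpose of the adjusted model: "Logistic regression will be performed to adjust potential confounding factors".
- Selection rule: "variables relevant to the models will be selected based on their clinical interest and/or a threshold" p-value "≤ 0.1 during univariate analysis". The variable against which the univariate test is run is not stated, and no candidate covariates are listed.
- Forced term: "The center will be automatically entered into the model". Center is also the stratification factor (Randomization).
- Rank: "The unadjusted analysis will be the primary analysis, and the adjusted analysis will be the complementary analysis".
- Secondary endpoints: "Multivariate approaches (logistic or linear regressions) will be performed using the same procedure".
- Later document: the section gives main principles only and says that "a specific protocol of the analysis will be provided a second time before the initialization of the study".

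**The concern.** A univariate p-value exists only once the trial data are in, so a model built on it cannot be written down beforehand. The and/or adds a second freedom: covariates could enter on clinical grounds alone, on the p-value alone, on either, or only on both. Each reading can give a different model.

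The stated purpose does not support a screen. Allocation is randomized 1:1 and stratified by center, so baseline differences between arms arise by chance. The sound reason to adjust is prognostic strength, which can be judged before the trial. Also, an odds ratio is conditional on the covariates in its model. Different selections therefore estimate somewhat different quantities, even without confounding.

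What is at stake is the standing of the adjusted results. Their confidence intervals are computed as if the model had been given, although the data chose it. If adjusted and unadjusted results differ, a reader of this open-label trial cannot separate the effect of prognostic adjustment from the effect of model choice. The secondary endpoints inherit the problem.

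**Working it through.** **1. The plan's own scale.** Inputs from Sample size, power and statistical methods: 20% against 14%, two-sided 5%, 80% power, 1300 patients needed, 1400 included to allow for 10% dropout.

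With pooled variance, n per arm = [1.960·√(2·0.17·0.83) + 0.842·√(0.20·0.80 + 0.14·0.86)]² / 0.06², which gives 615. With the continuity correction it is 647, or 1294 in total, in agreement with the stated 1300. After 10% dropout, 1400 × 0.9 = 1260, the size used below.

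**2. How often noise enters.** If k independent candidates are unrelated to the tested variable, each passes p ≤ 0.1 with probability 0.1. The expected number admitted is 0.1·k, and the chance of at least one is 1 − 0.9^k. The article does not give k, so a range is shown:

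| k (assumed) | expected noise variables | chance of at least one |
|---|---|---|
| 5 | 0.5 | 41% |
| 10 | 1.0 | 65% |
| 15 | 1.5 | 79% |
| 20 | 2.0 | 88% |

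If the test is against outcome, k counts only the non-prognostic candidates. If it is against arm, randomization makes every candidate noise in this sense, and k counts them all.

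**3. What the screen does to the treatment test.** Simulation with 3000 trials per scenario, n = 1260 and 10 independent normal covariates, of which 3 are prognostic and 7 are noise. Scenarios A and C use log odds ratios of 0.4, 0.3 and 0.15 per SD for the prognostic three; B uses 0.8, 0.6 and 0.15. A and B have no treatment effect. C has log odds ratio ln(0.14/0.86) − ln(0.20/0.80) = −0.429. The 20% rate is set at the covariate means, and center is not modeled. All of these choices are assumptions.

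| Proportion with p < 0.05 | A (null) | B (null) | C (power) |
|---|---|---|---|
| Unadjusted | 0.047 | 0.046 | 0.788 |
| Fixed set (the 3 prognostic) | 0.052 | 0.047 | 0.803 |
| Screen against outcome | 0.050 | 0.047 | 0.803 |
| Screen against arm | 0.048 | 0.042 | 0.790 |
| Smallest p of four models | 0.055 | 0.051 | 0.815 |

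The four models in the last row are the fixed set, the outcome-screened set, their union, and all 10 covariates. The Monte Carlo standard error near 0.05 is √(0.05·0.95/3000) = 0.004.

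**4. How variable the model is.** Screening against outcome produced 120, 107 and 117 different covariate sets in A, B and C. The screened log odds ratio differed from the unadjusted one with an SD of 0.030, 0.055 and 0.032. The SD of the unadjusted estimate was 0.137, 0.133 and 0.148. That movement includes what any adjustment for prognostic variables would cause, so it does not measure selection alone.

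**The case against.** The strongest reply is that little depends on this. The conclusion of the trial rests on an unadjusted chi-square or Fisher test with no covariates. The stratification factor is already forced into the adjusted model, which is labeled complementary, and the article assigns the robustness check to the per-protocol analysis. Section 3 of the working shows no material loss of type I error control or power. All of this stands, and it limits the size of the point.

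A second reply is that a fuller analysis protocol is promised before study start. This stands in part. That document can name the clinically chosen covariates and settle the and/or, and the absence of a list from an article is no fault. But the screen is stated as a principle, and a plan that kept it would still select from trial data.

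Three stronger readings are tempting, and the article does not support them:

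- A reader might infer that the model will be chosen after the results are seen. The article leaves room for this, but the promised protocol could close it.
- A reader might infer that known prognostic variables will be left out. Where either route suffices, the clinical-interest route admits them whatever their p-value.
- A reader might take 88% as the chance of a spurious covariate in this trial. It needs 20 noise candidates, a number the article does not give; with 5 it is 41%.

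**Conclusion.** The point holds as a minor one. The rule makes the adjusted estimates, for primary and secondary endpoints alike, depend on chance and on the reading of and/or, with intervals that take no account of selection. It is a method fixed badly, not a detail left for later.

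It would be wrong to conclude that the primary result is compromised: that test uses no covariates. Under the assumed scenarios, screening against outcome left type I error at 0.047 to 0.050, against 0.047 to 0.052 for a fixed set. Even the smallest p of four models gave only 0.051 to 0.055, and power was 0.803 with or without that screen. These figures rest on 10 independent candidates, the chosen prognostic strengths and n = 1260. A different number or correlation of candidates would change the detail. The gain from correcting the rule is a reproducible adjusted analysis, not a change in power or sample size.

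**What to change.** Delete the p ≤ 0.1 screen for primary and secondary models. In the analysis protocol promised before study start, name the covariates: center, plus a short list of baseline variables judged prognostic on clinical grounds and ascertained the same way in both arms before the intervention, for example age within population. If that protocol is already final, amend it before outcome data are seen.

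Do not use the number of medications at admission unless it comes from a source recorded identically in both arms before reconciliation. Under Control group, medical staff collect the list; under Experimental group, the pharmacist or pharmacy resident compiles it from several sources as part of the intervention. Adjusting for a count ascertained differently by arm could introduce bias.

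The list may differ by endpoint if each is fixed in advance, with fewer covariates for rare outcomes such as death.

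Suggested wording: *The adjusted models will include treatment, center and the baseline covariates listed for each endpoint in the analysis protocol. Covariates will not be added or removed on the basis of trial data.*

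Cost: wording only. Sample size, primary test and trial conduct do not change. The small downside is that the covariates must be agreed in advance.

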### Recruitment of participants and study setting

The recruitment will be performed in a pediatric department and a geriatric and internal medicine department. The methodological support will be provided by the Clinical Research Unit (Unité d’Aide Méthodologique à la Recherche Clinique, AP-HM, France). The central pharmacy of AP-HM is in charge of overall coordination of the study and implementation of interventions.

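### Randomization is stratified by center but the primary test ignores center: valid, but conservative and slightly less efficient if risk differs between strata

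*Protocol article*

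**What the plan says.** Under Randomization, the protocol article plans permuted blocks and states: "The randomization will be stratified by center". Allocation is 1:1. Under Recruitment of participants and study setting: "The recruitment will be performed in a pediatric department and a geriatric and internal medicine department". 'Center' is not defined. With one unit for each age group named, it most likely separates children from patients over 65, but that is an inference.

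Under Data analysis, the primary comparison of the two arms' day-30 proportions uses a chi-square or Fisher's exact test. A logistic regression follows, with center forced in and other covariates chosen for clinical interest or a univariate p-value of 0.1 or less. The order of the two is explicit: "The unadjusted analysis will be the primary analysis, and the adjusted analysis will be the complementary analysis".

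The sample size, under Sample size, power and statistical methods, rests on one overall risk per arm and not on risks by stratum: "the expected proportion of re-hospitalization and/or death in the standard group is 20% (worst case scenario". The target is a 6-point reduction, to 14%, for which the article asks for 650 evaluable patients per arm at 80% power and a two-sided 5% level.

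**The concern.** Blocking within center balances the arms on center, so differences in risk between centers largely drop out of the treatment contrast. A crude chi-square does not know this and still counts the between-center variation in its standard error. If center is prognostic, the test rejects less than 5% of the time under the null, and an interval for the difference built the same way is wider than it needs to be. The same patients would give somewhat more power under an analysis that respects the randomization.

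The article fixes this choice itself; it is not a detail left open for a later analysis plan. The complementary model is not a clean substitute, because its covariate set may depend on the trial data. The Discussion also concedes that power may suffer because the pharmacist is active in both groups, which is a reason not to give up precision that costs nothing.

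**Working it through.** **Inputs from the article:** control risk 20%, experimental risk 14%, two-sided 5%, 80% power, 650 per arm, 1:1 allocation.

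**Assumed, because the article gives neither:** the risk in each stratum and the share of children. All scenarios keep the control mean at 20% and apply a relative risk of 0.7 in both strata, so the overall risks stay at 20% and 14%.

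**1. The plan's own figure.** With p̄ = 0.17,
n = [1.96·√(2·0.17·0.83) + 0.8416·√(0.20·0.80 + 0.14·0.86)]² / 0.06² = (1.0412 + 0.4457)² / 0.0036 ≈ 614.1, so 615 per arm (1230).
With continuity correction: (614.1/4)·[1 + √(1 + 4/(614.1·0.06))]² ≈ 647 per arm (1294). The stated 1300 is therefore reproduced with the correction.

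**2. Overstatement of variance.** Let r be the mean within-stratum variance divided by the marginal variance, which is 0.20·0.80 = 0.16.
- 15%/25%, equal mix: (0.1275 + 0.1875)/2 = 0.1575; r = 0.984
- 8%/32%, equal mix: (0.0736 + 0.2176)/2 = 0.1456; r = 0.910
- 5%/35%, equal mix: (0.0475 + 0.2275)/2 = 0.1375; r = 0.859
- 10%/25%, one third children: 0.09/3 + 0.1875·2/3 = 0.155; r = 0.969

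The crude standard error is too large by the factor 1/√r. The crude test's type I error is 2·[1 − Φ(1.96/√r)].

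**3. Power at 650 per arm, no continuity correction.** Power = Φ[(0.06 − 1.96·s₀)/s₁]. Here s₁ is the true standard deviation of the difference under stratified allocation, and s₀ is the null standard error that the test uses. For the crude test s₀ = √(2·0.17·0.83/650) = 0.02084; for the stratified test it is built from within-stratum variances.

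Example, 5%/35%: the treated risks are 3.5% and 24.5%.
- s₁ = √[(0.1375 + 0.1094)/650] = 0.01949
- stratified s₀ = √(2·0.12484/650) = 0.01960
- crude: (0.06 − 0.04085)/0.01949 = 0.983, power 83.7%
- stratified: (0.06 − 0.03841)/0.01949 = 1.108, power 86.6%

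| Assumed control risk, children/elderly | SE too large by | Type I error, crude | Power, crude | Power, stratified |
|---|---|---|---|---|
| 20%/20% | 0% | 5.0% | 82.2% | 82.2% |
| 15%/25% | 0.8% | 4.8% | 82.3% | 82.7% |
| 10%/25%, one third children | 1.6% | 4.6% | 82.5% | 83.2% |
| 8%/32% | 4.8% | 4.0% | 83.1% | 85.0% |
| 5%/35% | 7.9% | 3.5% | 83.7% | 86.6% |

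The standard-error column is computed under the null.

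**4. Simulation check.** 200,000 trials per scenario at 650 per arm, with a common odds ratio instead of a common relative risk, gave power of 82.5% crude against 82.9% stratified at 15%/25%, and 83.9% against 86.8% at 5%/35%. The crude type I error was 4.8% and 3.4%; the stratified test stayed near 5.0%.

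**5. After dropout.** 1400 × 0.9 = 1260, or 630 per arm. Over the same scenarios, the uncorrected crude test has 81.0% to 82.5% power.

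**The case against.** The strongest reply is that nothing is broken. The crude test errs on the safe side, the loss is small, and it is a loss against a better test, not against the plan. At 15%/25% the gap is 0.4 points. A center-adjusted estimate will be reported anyway, so the dispute is only over which analysis is called primary. All of this stands, except that the adjusted model's data-dependent covariate choice makes it a poor stand-in for a stratified test fixed in advance.

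A reader might infer more than the article supports:
- *That risk is known to differ greatly between the age groups.* The article gives one overall 20% and no figure by stratum. The direction of the effect is certain once risks differ; its size is not.
- *That the trial is powered on a difference but reports only an odds ratio.* The article plans each arm's proportion with a 95% CI, so the absolute scale is covered. Odds ratios belong to the complementary models. An explicit CI for the difference is not mentioned.
- *That missing results by population or an interaction test are a defect.* The primary objective is one overall effect, and the article announces a separate, detailed analysis protocol where such analyses can be placed.
- *That separate conclusions for each population could be added at no cost.* At 8%/32% with a common relative risk of 0.7, the risk differences are 2.4 and 9.6 points. They would look heterogeneous although the relative effect is identical, and the sample size was not set for either population.

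**Conclusion.** The point holds as an efficiency matter. The plan stratifies allocation by center and then expressly sets center aside in its primary test. If center is prognostic, that test is conservative. Over assumed control risks of 15%/25% to 5%/35% with an equal mix, type I error is about 4.8% to 3.5%, the standard error is about 1% to 8% too large, and about 0.4 to 3 points of power are given up. If the strata have the same risk, the cost is zero.

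It would be wrong to read this as an invalid or underpowered primary analysis. Type I error is not inflated, and without continuity correction the crude test stays above 80% even at 630 per arm. With the correction, at 630 per arm and 8%/32%, simulated power is 79.9%, so the margin is thin; but that comes from the correction and the dropout allowance, not from ignoring center.

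The conclusion rests on the assumed stratum risks and mix, and on center separating the two age groups.

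**What to change.** Make the primary analysis a Cochran-Mantel-Haenszel test stratified by center, and also by pediatric/geriatric population if that is not the same thing. Report a Mantel-Haenszel risk difference with a 95% CI, and keep the crude chi-square as supportive. State what 'center' means. Results by population may be shown descriptively, with a note that the trial is not powered for them.

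With 1:1 allocation within each stratum, the Mantel-Haenszel weights are proportional to stratum size. The point estimate will therefore be almost the same as the crude difference; what changes is mainly its standard error. The cost is a change of wording, made before any comparison of outcomes by arm. Center is already recorded for randomization, and no extra data or patients are needed.
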